#### Caregiver evaluation

The retrospective patient Feedback Questionnaire exists in a family caregiver version, offering the opportunity to explore the duration of effects from a caregiver perspective [1, 81]. In case of prior consent, the caregivers’ evaluation of treatment quality will therefore be assessed after the treatment (T1) and 8–16 weeks later (T2).

### Data monitoring and management

Data collection and conduction of trial will be monitored by the principal investigators. Adverse or unintended effects of interventions or conduct will be reported and managed in standard palliative care. In order to protect confidentiality, all data and biomaterial will be collected and stored for 10 years in a pseudonymized form at the Center for Psychosocial Medicine at University Hospital Heidelberg. Only the principal investigators will have access to the assignment key. No third parties are allowed inspection of personal data. After the end of the research project, data will be published in online repositories in an anonymized form.

### Data analysis

Data will primarily be analyzed within an intention-to-treat approach. Results will be tested for robustness in comparison to a per-protocol-analysis (sensitivity analyses). Primary hypotheses tests will be conducted with analyses of co-variance (ANCOVA). The study design contains two independent variables to predict variance in the primary outcome: 2 groups (between-subjects factor) * 2 measurement times (within-subjects factor). In order to increase statistical power, the ANCOVA models will treat pre-intervention baseline data as a covariate and group assignment as a fixed factor [82]. The following primary hypotheses will be tested in a confirmatory ANCOVA with a type-I error probability of α = 0.05: There is a significant effect of group assignment on psychological quality of life after the intervention (while controlling for baseline differences). Group differences in the changes in secondary outcomes will be tested accordingly without adjustment for multiple testing, due to the a priori distinction between primary and secondary outcomes and the likelihood of the outcomes to correlate.

In addition to statistical significance, we will report descriptive statistics and effect size estimates. Biomarker analysis will be conducted by use of multilevel modeling, as repeated observations are nested within participants, and experience from previous research revealed substantial heterogeneity in slopes and trajectories among severely ill patients [77, 83]. Multilevel modeling can be further used for subgroup analysis (e.g. gender differences), for moderator analysis (e.g. the influence of patient distress), and to account for confounding variables (e.g. baseline differences, sex, age). Qualitative data from session S3 will be recorded, transcribed, coded, and analyzed in accordance with Mayring’s approach to qualitative content analysis [84].

### Sample size

Sample size calculations for this study are adjusted for intervention effects on psychological quality of life (i.e. the primary outcome). A systematic review [85] suggests that medium-sized effects are most likely to be expected for the impact of music therapy on psychosocial outcomes in palliative care. Our own studies support this assumption finding effect sizes varying between *d* = 0.35 and *d* = 0.80 for generic quality-of-life measures [40]. Recent articles [82, 86] on sample size calculations emphasize the superiority of ANCOVA models for analyzing the results of RCTs over the repeated-measures ANOVA approach, as the inclusion of pretest values as a covariate increases statistical power. Assuming statistical power of (1- α) = 0.8, type-I error probability of α = 0.05, and a correlation between covariate and outcome of ρ = 0.6, a total sample size of *N* = 84 is required to detect medium sized effects of *d* = .50 between groups [86]. With an expected dropout rate of approximately 25%, *N* = 104 participants need to be recruited for this study.

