**Methods:**

In a design with two parallel arms, 104 patients at two palliative care units will be randomly assigned to three sessions of either SOL (experimental group) or relaxation exercises (control group). Improvements in the psychological domain of quality of life will be the primary endpoint, while secondary outcomes encompass spiritual well-being, ego-integrity, overall quality of life, and distress. Additionally, caregivers will be asked to provide feedback about the treatment. Assessment of biopsychological stress markers and qualitative analysis of perceived strengths and weaknesses will complement data collection.

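### Recruiting 104 patients with the stated dropout of about 25% leaves 78, not the required 84, so power is about 78% rather than 80% if dropouts give no primary outcome

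*Protocol article*

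**What the plan says.** The Sample size section sets out the calculation for the primary outcome, psychological quality of life, analysed by ANCOVA with the baseline value as covariate. Its inputs are:

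- power: "Assuming statistical power of (1- α) = 0.8";
- error rate and correlation: "type-I error probability of α = 0.05, and a correlation between covariate and outcome of ρ = 0.6";
- effect: "medium sized effects of *d* = .50 between groups".

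From these, "a total sample size of *N* = 84 is required". The next sentence moves from that requirement to the recruitment target: "With an expected dropout rate of approximately 25" per cent, it concludes that "104 participants need to be recruited for this study". The Methods paragraph of the abstract gives the same target: "104 patients at two palliative care units will be randomly assigned". Nothing else in the article explains the step from 84 to 104.

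**The concern.** The required number, the expected loss and the recruitment target stand in two consecutive sentences and cannot all hold. A quarter of 104 is 26, and removing 26 leaves 78. The target therefore falls short of the plan's own requirement at the plan's own dropout rate.

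At stake is the accuracy of the power statement for the single confirmatory test. The Discussion tells readers how to interpret a non-significant result against an active control, and expects that control to reduce the observed difference. A reader who follows that advice needs to know the power the design has under its stated assumptions.

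**Working it through.** **Inputs.** All come from the Sample size section unless noted.

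- d = 0.50, ρ = 0.6, α = 0.05, power 0.80, required N = 84, dropout about 25%, recruited N = 104.
- Sidedness is not stated. I assume two-sided, because it reproduces 84; a one-sided test would need 64 by the normal approximation.
- The allocation ratio is not stated. I assume 1:1 in the two arms.
- Analysis: ANCOVA with one covariate (Data analysis section).

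**Step 1: reproduce 84.** Adjusting for baseline reduces the residual SD by the factor √(1 − 0.6²) = 0.8.

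- Normal approximation, per arm: 2 × (1.96 + 0.8416)² × (1 − 0.36) / 0.25 = 40.2, rounded up to 41, or 82 in total.
- Noncentral t with N − 3 degrees of freedom and noncentrality (d / 0.8) × √(N/4): N = 82 gives 79.8% and N = 84 gives 80.8%. The smallest even total reaching 80% is 84.
- A two-sample t-test size of 64 per arm, times (1 − ρ²), is 40.96. Rounded up to 41, plus one per arm, this is 42 per arm, again 84.

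The requirement of 84 is therefore sound.

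**Step 2: the dropout step.**

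- Retained from 104 at 25% loss: 104 × 0.75 = 78, which is 84 − 78 = 6 short.
- Standard inflation: 84 / (1 − 0.25) = 112.
- Largest loss that leaves 84: 1 − 84/104 = 19.2%.
- Multiplying instead of dividing gives 84 × 1.25 = 105, close to 104, and 104 is 13 full blocks of 8. This may be how the figure arose, but it is conjecture; the article does not link the block size to the target, and the inconsistency does not depend on it.

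**Step 3: what it costs** (d = 0.50, ρ = 0.6, two-sided α = 0.05).

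| Patients with outcome | Power, noncentral t | Power, normal approximation | Effect detectable at 80% power (noncentral t) |
|---|---|---|---|
| 84 | 80.8% | 81.7% | 0.495 SD |
| 78 | 77.8% | 78.8% | 0.514 SD |

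**Step 4: other dropout rates with 104 recruited** (noncentral t): 20% gives 80.4%, 22% gives 79.4%, 25% gives 77.8% and 30% gives 74.8%.

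**The case against.** **The loss is small.** Against the nominal 80% it is 2.2 points by noncentral t and 1.2 by the normal approximation. Uncertainty in the inputs matters as much: with ρ = 0.63, 78 patients give 80.1%, while with ρ = 0.55 even 84 give 77.4%. The section itself cites effects from d = 0.35 to d = 0.80. The slip biases no estimate and leaves the type-I error unchanged. This stands, and it makes the point minor.

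**A patient who drops out may still be measured.** The Interventions section provides for self-report data on the primary and secondary outcomes from patients who stop early, if they consent, and the primary analysis is by intention to treat. The article does not define dropout as a missing primary outcome. If 6 of the 26 expected dropouts gave usable post-intervention data, 84 would be reached. This stands in part. Recovery depends on consent, patients may ask for their data to be deleted, and no recovery rate is given. The calculation also uses dropout as its reason to recruit beyond 84, which implies that those patients are counted as lost.

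**The word "approximately" may give room.** Some, but 19% is not a natural reading of about 25%.

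**Stronger readings that the article does not support.** A reader might infer that the trial will certainly miss 80% power; given the provision for data after stopping, the article shows only that the stated allowance does not secure it. A reader might infer that 112 is the only remedy; it is the standard inflation of 84, but 83 patients already give 80.3%, and outcome data from patients who stop early are another route. A reader might infer that a registered power figure is wrong; the article says only that the outcomes were registered, and the registry entry is not at hand.

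**Conclusion.** The inconsistency is real and minor. The requirement of 84 reproduces; the step to 104 does not match a dropout of about 25%. If dropouts contribute no primary outcome, 78 patients remain, power for d = 0.50 is about 78%, and 80% power is reached at about 0.51 SD. This rests on a two-sided test, equal allocation and ρ = 0.6 as stated. The gap narrows with every patient who stops early but still provides the outcome. It does not undermine the design or the analysis; it means that the stated power, dropout and sample size need to be brought into line.

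The label (1- α) for power is a clerical slip. With α = 0.05 in the same sentence, 1 − α would be 0.95, so (1- β) is clearly meant. It adds nothing to the severity.

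**What to change.** Keep 104 and restate the sentence in one of two ways:

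- 25% dropout from 104 leaves 78 evaluable patients, with power of about 78% for d = 0.50 (80% for d = 0.51); or
- 104 allows for a dropout of about 19%, if the investigators can justify that rate.

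The first needs no new assumption. If the investigators expect outcome data from some patients who stop early, they can say so and give the rate they assume. Recruiting 112 would restore the standard allowance for 25%, but a gain of about three points of power is a weak reason to enrol more terminally ill patients. Correct (1- α) to (1- β) in the same edit.

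The cost is one or two sentences in the Sample size section and a slightly less favourable power or dropout figure. The abstract's 104 can stay.

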## Discussion

We present the protocol of a randomized controlled trial on the emotional, spiritual, and biological effects of the “Song of Life” intervention for patients receiving palliative care. Our decisions for the chosen research methods are the result of intensive, critical and interdisciplinary discourse between researchers and clinicians from psychology, medicine, and music therapy. Although we are confident to have designed a robust and sound approach to study the effects of the SOL intervention, we would like to discuss some potential methodological pitfalls.

First, the design of an appropriate control intervention is crucial for the interpretation of effects. Most studies on psychosocial interventions in palliative care compare the actual treatment to a “standard care” or “treatment as usual” group. While it is more likely to identify significant effects in comparison to a group that does not receive any additional treatment, these effects cannot be causally attributed to the intervention, as attentional, expectancy and other biases can play a role. Moreover, it can be argued that it is unethical to include terminally ill patients in a study and then withhold a potentially effective treatment. In a previous trial, we therefore compared a music therapy relaxation exercise to a prerecorded verbal relaxation exercise [87]. While this was a methodological improvement over many studies in the field, we still could not rule out the possibility that the personal attendance to the patient in the experimental group contributed to the observed effects. Hence, we decided to use an active and effective control intervention carried out by trained therapists in the present study. We did not include a third “standard care” arm as this could raise ethical concerns and would have further increased the required number of participants.

We are aware that direct comparison to an active control treatment will diminish the magnitude of observed effects because we expect the relaxation exercises to lead to substantial improvements as well. This could become particularly challenging, as our pilot study showed only medium-sized effects from pre to post for the unmodified version of the SOL [50]. However, our response was not to dilute the study design, but to put effort in optimizing the treatment and selecting appropriate outcomes. We would like to encourage all readers to interpret the upcoming results of the study accordingly: Non-significant findings would not mean “not effective” but rather “not more effective than relaxation exercises”, while significant findings in the expected direction would mean “even more effective than relaxation exercises”.

We believe the major strengths of this study to be the innovative intervention that was specifically designed to address the needs of patients nearing the end of life and the comprehensive assessment plan including emotional, spiritual, and biological outcomes. Moreover, the comparison to an active control treatment is unique in the study of music therapy in palliative care and will significantly reduce the likelihood of attention and expectation bias [88]. Finally, we would like to emphasize that the present paper is an a priori study protocol, which means that the primary and secondary outcomes were registered and made public before the first patient was randomized which will diminish the risk of “*p*-hacking” and reporting bias.

The present study will help to understand the potential of psychosocial interventions for terminally ill patients and will particularly contribute to the evidence base of creative-arts based therapies in palliative care.

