### Study design

The study utilizes a prospective, randomized controlled design with two parallel arms. Patients will be randomly assigned to three sessions of either music therapy (EG) or relaxation exercises (CG). We will not give information about which of the two alternative treatments is the experimental and which is the control condition. Hence, patients will be blinded with regard to the study hypotheses. It will not be possible to blind the therapists and outcome assessors, but all data will be assessed by persons different than the study therapists (i.e. study nurse, doctoral student). We will use a computer-based block randomization procedure with a block size of 8. A random sequence for group assignment will be created before the first patient is randomized. Based on this sequence, we will use the SNOSE-method [46] to conceal allocation. We expect benefits and improvements in both treatment groups with a superiority of the SOL intervention. The study design is summarized in Fig. 1.

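### The Discussion reads a non-significant result as no advantage over relaxation, which a superiority test of this size cannot show

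*Protocol article*

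**What the plan says.** The Study design section sets up a superiority comparison against an active control: "We expect benefits and improvements in both treatment groups with a superiority of the SOL intervention". The Data analysis section tests the primary outcome in a "confirmatory ANCOVA with a type-I error probability of α = 0.05", with the baseline value as covariate. The hypothesis is worded without direction: "There is a significant effect of group assignment on psychological quality of life after the intervention". Beyond the p-value, the same section promises this: "In addition to statistical significance, we will report descriptive statistics and effect size estimates".

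The Sample size section arrives at N = 84, which "is required to detect medium sized effects of *d* = .50 between groups", using a baseline-outcome correlation of 0.6. It plans to recruit 104 because about 25% are expected to drop out. It also cites effects of d = 0.35 to 0.80 from the team's own earlier studies on generic quality-of-life measures.

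The Discussion says that the active control will make the observed difference smaller. It then tells readers how to take a null result: "Non-significant findings would not mean “not effective” but rather “not more effective than relaxation exercises".

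**The concern.** The sentence is right that a null result against an active control does not show SOL to be ineffective. What it offers in place of that conclusion is also unsupported. A superiority test that does not reject says that the data are compatible with no difference. It does not say that the data are incompatible with a worthwhile one. Which differences have been ruled out can be read only from the confidence interval.

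At stake is the conclusion drawn after a null result. A reader who follows the stated reading would conclude that SOL has no advantage over relaxation, even when the interval still contains the very effect for which the trial was sized.

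**Working it through.** **Inputs.** From Sample size: d = 0.50, correlation 0.6, alpha 0.05, power 0.80 (printed as "Assuming statistical power of (1- α) = 0.8" and read here as 1 − β), N = 84, 104 recruited, about 25% dropout, and the earlier-study range starting at d = 0.35. Assumed: a two-sided test, because the hypothesis is non-directional, and 1:1 allocation, because no ratio is stated.

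**Step 1: reproduce N = 84.** With the baseline as covariate, the residual SD in outcome-SD units is √(1 − 0.6²) = 0.8.
- Normal approximation: n per arm = 2 × (1.960 + 0.842)² × 0.64 / 0.25 = 40.2, so 41 per arm and 82 in total.
- Noncentral t with N − 3 degrees of freedom: the smallest even N with power of at least 0.80 is 84 (power 0.808).
- A one-sided test would give 64, which does not match.

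The stated figure reproduces, and this supports the two-sided reading.

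**Step 2: precision of the adjusted difference.** SE = 0.8 × √(4/N), and the 95% half-width is t(0.975, N − 3) × SE.
- N = 84: SE = 0.8 × √(4/84) = 0.1746; half-width = 1.990 × 0.1746 = 0.347 SD.
- N = 78 (104 × 0.75, if all dropouts lack outcome data): SE = 0.1812; half-width = 1.992 × 0.1812 = 0.361 SD.

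The half-width is also the smallest estimate that reaches significance.

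**Step 3: non-significant estimates that do not exclude d = 0.50.** The upper limit reaches 0.50 once the estimate is at least 0.50 minus the half-width.
- N = 84: 0.50 − 0.347 = 0.153, so estimates from about 0.15 to 0.35 SD.
- N = 78: 0.50 − 0.361 = 0.139, so estimates from about 0.14 to 0.36 SD.

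For example, an estimate of 0.20 SD at N = 84 has the interval 0.20 ± 0.347, that is −0.15 to 0.55. It is not significant, and it contains both zero and the design effect.

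**Step 4: how often a real advantage gives p ≥ 0.05.** Noncentral t with noncentrality d / SE:

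| True d | N = 84 | N = 78 |
|---|---|---|
| 0.50 | 19% | 22% |
| 0.35 | 49% | 52% |

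At N = 84 the noncentralities are 0.50 / 0.1746 = 2.86 and 0.35 / 0.1746 = 2.00.

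**The case against.** The sentence stands in the Discussion, not under Data analysis, and it is addressed to readers. Its main purpose is cautionary: the comparator is an active treatment, so a null result must not be taken to mean that SOL does nothing. It can be read loosely as only naming that comparator. It leaves the test and its type I error unchanged, and the plan promises effect sizes beside p-values. A superiority trial needs no equivalence margin, and an article may leave interval reporting to a fuller document. The 19% at the design effect is the ordinary type II error of a trial with about 80% power. The 0.35 comes from other measures in other studies.

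All of this stands, and it limits the point to interpretation. It does not rescue the wording. The article says what a non-significant finding would mean, and what it says is that SOL is not more effective. The fault lies in that stated conclusion, not in a missing margin or interval.

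A reader might go further and infer that the companion phrase, which calls a significant result evidence that SOL is even more effective than relaxation, fails because no untreated arm shows that the control works. The Discussion does describe the comparator firmly: "we decided to use an active and effective control intervention carried out by trained therapists in the present study". But it also acknowledges and justifies the absence of a standard-care arm, presents benefit from relaxation as an expectation, and confines the comparison to SOL against relaxation. That inference is not made here.

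**Conclusion.** The stated reading of a null result is wrong and should be corrected. The matter is of moderate severity. With N = 84, a correlation of 0.6, two-sided alpha 0.05 and equal allocation, any estimate between about 0.15 and 0.35 SD would be labelled as no advantage while d = 0.50 remained inside its interval. Non-significance has a probability of about 19% if the true d is 0.50 and about one half if it is 0.35. Using 78 instead of 84 changes these figures only slightly, and the conclusion does not depend on it. The analysable number need not fall to 78, because the primary analysis is by intention to treat and outcomes will be sought from consenting patients who stop early.

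Three stronger readings are not supported:
- That the investigators are committed to reporting an advantage as disproved. The Data analysis section contains no such rule.
- That a null result is the probable outcome. The Discussion expects a smaller effect against the active control but gives no amount.
- That the trial needs an equivalence margin or more patients. That would follow only if it set out to demonstrate the absence of an advantage, and it does not.

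**What to change.** Reword the Discussion sentence along these lines: *a non-significant result would not mean that SOL is ineffective; it would mean that superiority over the relaxation exercises was not shown.* Add that such a result will be interpreted from the baseline-adjusted mean difference and its 95% confidence interval, with a statement of which differences the interval excludes. Say that a medium-sized advantage is absent only if the upper limit lies below the design effect of d = 0.50. At N = 84 and on the planning inputs, this requires an estimate below about 0.15 SD.

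The cost is one reworded sentence and an interval that the planned ANCOVA already produces. The endpoint, test, alpha and sample size do not change.
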